**Population:**

**Phase 3: Full Trial**

Approximately 500 crack smokers and 500 injectors will be recruited to participate in the longitudinal component of the study (i.e. baseline and follow-up assessments) Of these, approximately 250 crack smokers and 250 injectors with CES-D scores ≥16 will be randomly assigned to either the depression intervention or control condition.

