# Power calculations

# The main outcomes of interest are changes in injection and sexual risk behavior and in level of depressive symptoms. A sample size of 200 in each group is assumed for comparisons of sex risk behaviors and depressive symptoms after two years of follow-up with a 10% attrition rate per year. Only half of the sample will be IDUs, and it is assumed that there will be a sample size of 100 per group with the same attrition rates. There will be approximately 50 cohorts (25 intervention cohorts and 25 control cohorts) of with approximately 8 members with complete data at the end of the two years. The power was calculated for an assessment of intervention effectiveness at the end of the study, when sample sizes will be smallest and thus underestimates likely power for comparisons made earlier in the study. Power calculations were done using NCSS/PASS software. Based on the SHIELD study (IRB# H.30.00.07.17.A), we would expect an average CES-D score of 26.7 and variance of 8.3, given the selection methods proposed in the present study. We estimated power with a 2-sided test, setting the alpha at 0.05, with a total sample size of 400. We expect a small amount of correlation due to intervention group (0.02 in the SHIELD Study). A difference between the two groups post intervention on mean CES-D score of 2.0 provides sufficient statistical power.

|  | **Intercluster correlation** | | |
| --- | --- | --- | --- |
| **Difference in mean CES-D score** | 0.00 | 0.02 | 0.05 |
|  | **Power** | | |
| 2.0 | 0.92 | 0.88 | 0.83 |
| 3.0 | 0.99 | 0.99 | 0.99 |
| 4.0 | 1.00 | 1.00 | 1.00 |

Prior studies suggest a larger effect size for intervention effects on injection as compared to sexual risk behaviors. Consequently, despite the smaller sample size for injection risk comparisons, we expect analyses of the two outcomes to have similar statistical power. We based estimates of expected reduction in risk behaviors on the SHIELD study, creating composite scores for injection risk behavior (needle and cooker sharing and frequency of injecting) and sexual risk behavior (9 risk behaviors). The injection risk score had a mean of 11.6 (SD=4.5). The sex risk composite score had a mean of 1.9 (SD=1.8).

|  | Intercluster correlation | | |  | Intercluster correlation | | |
| --- | --- | --- | --- | --- | --- | --- | --- |
| Diff. in mean injection risk score | 0.00 | 0.02 | 0.05 | Diff. in mean sex risk score | 0.00 | 0.02 | 0.05 |

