**Inclusion and Exclusion Criteria**

**Phase 3: Full Trial**

There are 2 tiers of inclusion and exclusion criteria. The first tier is eligibility criteria for the longitudinal study which will be determined through a brief screening assessment. The second tier is eligibility for the RCT which will be assessed during the baseline survey.

Inclusion criteria for longitudinal study include:

1. 18-55 years old
2. HIV Risk Behavior:

3a. Injected drugs more than 3 times in the past week OR

3b. Smoked crack in the past 6 months AND had 1 of the following sex risks in the past 6 months:

- - - 2 or more sex partners
    - Had a sex partner who injected drugs
    - Had a sex partner who smoked crack
    - Had a sex partner who was HIV+

1. Willingness to attend group sessions

Exclusion criteria for longitudinal study include:

1. Enrolled in another HIV behavioral intervention or depression study in past the 3 years
2. Enrolled in another Lighthouse study in past the 5 years
3. Enrolled in the formative research (Phase 1) or pilot (Phase 2) of the current project.

The 2^nd^ tier will be for randomization into the RCT. These criteria will be assessed during the baseline survey.

Inclusion criteria for the RCT include:

1. Met inclusion criteria for longitudinal study (see above)
2. Have depressive symptoms as determined by CESD scores 16 or greater at baseline assessment

Exclusion Criteria:

1. Severe levels of depression as determined by CESD score ≤40
2. Symptoms of mental illness that require treatment (i.e., actively manic, actively psychotic, DSM IV Axis II Cluster B such as histrionic, borderline, anti-social)

Individuals who are excluded based on mental illness will be given referrals to local agencies that provide mental health services.

In addition, individuals who are disruptive to the group will be removed from the group session and provided with other referrals.

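### The CES-D power rests on a spread of 8.3 that is mislabelled as a variance, tied to no visit and not shown to belong to the post-intervention score; the printed power does not follow from it on the stated cohorts

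*Protocol*

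**What the plan says.** The Power calculations section of the Protocol takes its CES-D inputs from the investigators' prior study: "we would expect an average CES-D score of 26.7 and variance of 8.3, given the selection methods proposed in the present study". The remaining inputs are:

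- Test and total sample: "We estimated power with a 2-sided test, setting the alpha at 0.05, with a total sample size of 400".
- Clusters: "There will be approximately 50 cohorts (25 intervention cohorts and 25 control cohorts) of with approximately 8 members with complete data".
- Clustering: "We expect a small amount of correlation due to intervention group (0.02 in the SHIELD Study").

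The table gives power of 0.92, 0.88 and 0.83 for a 2.0-point difference at ICC 0.00, 0.02 and 0.05. The text concludes: "A difference between the two groups post intervention on mean CES-D score of 2.0 provides sufficient statistical power". It says the calculation applies to the end of the study.

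The same instrument decides entry. The Population section says that "approximately 250 crack smokers and 250 injectors with CES-D scores ≥16 will be randomly assigned", and the RCT inclusion criterion reads "Have depressive symptoms as determined by CESD scores 16 or greater at baseline assessment". The RCT exclusion list also removes severe depression, printed as a CES-D score of 40 or less. As printed, that conflicts with the inclusion of scores of 16 or more.

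**The concern.** Two things about the 8.3 do not fit its use.

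First, the label. A variance of 8.3 means an SD of 2.9. That is implausibly small beside a mean of 26.7 and incompatible with the printed power.

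Second, the population and the visit. The figure is qualified by the way people are selected, and they are selected on a minimum CES-D score at baseline. A cut-off on a variable narrows its spread at that visit. The powered comparison is of later scores, which may fall below 16. If 8.3 is the SD of the entry score, an unadjusted post-intervention comparison would face a wider spread. The Protocol names no visit, gives no follow-up SD and gives no baseline-to-follow-up correlation, so a reader cannot tell whether the input belongs to the endpoint.

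At stake is the sentence declaring 2.0 points sufficiently powered. If it is wrong, a real 2-point benefit would be missed more often than stated, and a null result would be read as stronger evidence of no effect than it is.

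**Working it through.** **Inputs from the Protocol.** Difference d = 2.0; two-sided alpha 0.05; k = 25 cohorts per arm; m = 8 completers per cohort, so n = 200 per arm; ICC 0.00, 0.02 or 0.05; spread 8.3.

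**Formula.** SE = SD × √[(2/n) × (1 + (m − 1) × ICC)]. Power comes from the non-central t distribution with 2k − 2 degrees of freedom and non-centrality d/SE.

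**Step 1: reproduce the printed row (0.92 / 0.88 / 0.83).**

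| Reading | ICC 0.00 | 0.02 | 0.05 |
|---|---|---|---|
| Variance 8.3 (SD = √8.3 = 2.88), 25 cohorts per arm | 1.00 | 1.00 | 1.00 |
| SD 8.3, 25 cohorts of 8 per arm (as stated) | 0.66 | 0.60 | 0.53 |
| SD 8.3, 50 cohorts of 8 per arm | 0.921 | 0.885 | 0.827 |

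For the second row at ICC 0.02, the design effect is 1 + 7 × 0.02 = 1.14. Then SE = 8.3 × √(0.01 × 1.14) = 0.886 and the non-centrality is 2.0/0.886 = 2.26. The critical value is 2.011 on 48 df, and power is 0.60.

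With SD 8.3 the table therefore needs 400 per arm, not 200. The injection-risk rows show the same doubling. For 1.0 point, SD 4.5 with 200 per arm in clusters of 4 (normal approximation) gives 0.60/0.58/0.54, against the printed 0.60/0.57/0.54; the text states 100 per arm. The sex-risk rows are nearer to 400 than to 200 per arm but match neither exactly.

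**Step 2: detectable difference on the stated cohorts.** For 80% power at ICC 0.02, d ≈ (2.011 + 0.849) × 0.886 = 2.53 points at SD 8.3. This allows nothing for entry selection.

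**Step 3: what entry selection could add (assumptions).** Let s be the SD in the unselected population, r the baseline-to-follow-up correlation, and v the entry-score SD after selection. Under a linear normal model, the follow-up SD among those selected is √[s²(1 − r²) + r²v²]. The residual SD after baseline adjustment is s√(1 − r²). The Protocol gives neither s nor r.

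| Assumed s, r, v | Follow-up SD | Power, 2.0 points, ICC 0.02, 25 × 8 per arm |
|---|---|---|
| 10, 0.7, 8.3 | 9.2 | 0.51 |
| 12, 0.3, 8.3 | 11.7 | 0.35 |
| 13.4, 0.7, 6.2 (normal cut to 16–40) | 10.5 | 0.42 |
| 13.4, 0.5, 6.2 (normal cut to 16–40) | 12.0 | 0.33 |

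First row: √(100 × 0.51 + 0.49 × 68.89) = √84.8 = 9.2. Detectable differences at 80% power run from 2.86 × 0.982 = 2.81 (SD 9.2) to 2.86 × 1.281 = 3.66 points (SD 12.0).

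**Step 4: baseline adjustment.** For s = 10 to 12 and r = 0.3 to 0.7, the residual SD runs from 7.1 (s = 10, r = 0.7) to 11.5 (s = 12, r = 0.3). With the ICC held at 0.02, power runs from 0.73 down to 0.36. The residual SD equals 8.3 when r = √(1 − (8.3/s)²), that is 0.56 at s = 10, 0.66 at s = 11 and about 0.78 at s = 13.4. Adjustment can therefore cancel the widening or leave most of it in place.

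**The case against.** The strongest reply is that no visit is named. The wording would also fit the later scores of prior-study participants who met this trial's entry rule, which is the right input, and the section says the calculation is for the end of the study. The size of 8.3 does not settle the matter. A normal distribution with mean 13.4 and SD 14.5, cut only at 16, has mean 26.7 and SD 8.3, as an entry score might. But if the eligible range were 16–40, even a flat distribution would have an SD of only 7.2, so 8.3 would be too wide for an entry score. Nor do the documents fix a population median of 16. The Population section gives the number randomised, which also depends on other exclusions and on who attends. This objection stands. A reader might infer that the endpoint SD is definitely understated, or that true power is 0.33 to 0.41; the documents do not support either.

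It is also fair that the outcomes are worded as changes and that the Statistical Analysis Plan section allows covariate adjustment. At 200 per arm, the printed row would follow from an SD of about 5.9 (normal approximation), which is the residual of 8.3 at a correlation of √(1 − (5.94/8.3)²) = 0.70. But the Protocol states no correlation and fixes no CES-D model, so this cannot be taken as the basis of the table.

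The last reply is that the largest demonstrated gap comes from the cohort count. That is true, but correcting the count alone would leave a mislabelled input of unknown visit in the calculation.

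**Conclusion.** Wrong as written. From the Protocol's own figures, 8.3 cannot have been used as a variance, and as an SD it yields 0.66/0.60/0.53 on 25 cohorts of 8 per arm, not 0.92/0.88/0.83. The sentence calling 2.0 points sufficiently powered does not follow from the stated inputs.

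The effect of entry selection is conditional. If 8.3 is the entry-score SD and the comparison is unadjusted, the follow-up SD would be larger and power below 0.60 at ICC 0.02, at about 0.51 to 0.33 for follow-up SDs of 9.2 to 12.0. That range rests on a normal model, an assumed population SD of 10 to 13.4 and an assumed correlation of 0.3 to 0.7. Baseline adjustment could remove some or all of the loss. What is established is that the spread is mislabelled and not shown to be that of the powered endpoint.

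**What to change.** In Power calculations:

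1. Label 8.3 as an SD and state the visit at which it was measured.
2. Reconcile the exclusion printed as a CES-D score of 40 or less with the inclusion of scores of 16 or more, because the entry range determines which prior-study participants are relevant.
3. Among prior-study participants in that range, take the SD of the follow-up CES-D. If the analysis adjusts for baseline, take the residual SD instead and state the correlation.
4. Recompute the CES-D rows for 25 cohorts of 8 per arm and restate the sentence on sufficient power, giving the difference that is detectable.

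The cost is one rerun of a power table, using data from the prior study on which the Protocol already draws, and a few sentences of wording. No extra patients are needed. The stated power becomes less favourable, unless a documented residual SD supports the present figures.

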|  | **Power** | | |  | **Power** | | |
| 1.0 | 0.60 | 0.57 | 0.54 | 0.25 | 0.54 | 0.49 | 0.43 |
| 1.5 | 0.91 | 0.89 | 0.87 | 0.50 | 0.98 | 0.97 | 0.94 |
| 2.0 | 0.99 | 0.99 | 0.98 | 0.75 | 1.00 | 1.00 | 1.00 |
| 2.5 | 1.00 | 1.00 | 1.00 | 1.00 | 1.00 | 1.00 | 1.00 |

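### The power tables do not follow from the stated design: with 25 cohorts of about 8 per arm, unadjusted power for a 2-point CES-D difference is about 0.60 at an intracluster correlation of 0.02, not 0.88

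*Protocol*

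**What the plan says.** The Power calculations section gives the size of the trial in three ways that agree:

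- By arm: "A sample size of 200 in each group is assumed for comparisons of sex risk behaviors and depressive symptoms after two years of follow-up".
- By cluster: "There will be approximately 50 cohorts (25 intervention cohorts and 25 control cohorts"), each with about 8 members who have complete data.
- In total: "We estimated power with a 2-sided test, setting the alpha at 0.05, with a total sample size of 400".

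For the injection outcome only half the sample counts, and "it is assumed that there will be a sample size of 100 per group with the same attrition rates", which is about 4 injectors per cohort.

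On spread, the section says of the CES-D that "we would expect an average CES-D score of 26.7 and variance of 8.3". It gives SDs of 4.5 for the injection score and 1.8 for the sex-risk score. The expected correlation within intervention groups is 0.02.

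The CES-D table prints 0.92/0.88/0.83 for a difference of 2.0 at correlations of 0.00/0.02/0.05. The first row of the combined risk table, injection on the left and sex risk on the right, reads "1.0 | 0.60 | 0.57 | 0.54 | 0.25 | 0.54 | 0.49 | 0.43". The section concludes: "A difference between the two groups post intervention on mean CES-D score of 2.0 provides sufficient statistical power".

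**The concern.** The printed powers are too high for 200 per arm. With SD 8.3, a 2.0-point difference is 2.0/8.3 = 0.24 SD. Two arms of 200 give about two-thirds power for that even before any clustering, yet the table prints 0.92.

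All three scores are named as main outcomes, and the case for the sample size rests on these tables. If they are wrong, ethics and monitoring reviewers have been told that the trial is well powered for an effect it would miss about four times in ten.

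**Working it through.** **Inputs, all from Power calculations.** Two-sided alpha 0.05. K = 25 cohorts per arm. m = 8 completers per cohort for CES-D and sex risk, m = 4 for injection (100/25). SDs 8.3, 4.5 and 1.8. Intracluster correlation (ICC) 0, 0.02 and 0.05.

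**Method.** Unadjusted two-sample comparison of means with clustering:

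- Design effect: DE = 1 + (m − 1) × ICC
- Standard error: SE = SD × √(2 × DE / (K × m))
- Power from the noncentral t with 2(K − 1) degrees of freedom and noncentrality difference/SE

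**Step 1: CES-D, difference 2.0, ICC 0.02, stated design.** DE = 1 + 7 × 0.02 = 1.14. SE = 8.3 × √(2 × 1.14/200) = 0.886. Noncentrality = 2.0/0.886 = 2.26. With 48 df the critical value is 2.01, and power is 0.60. The table prints 0.88. The normal approximation gives 0.62, so the choice of reference distribution does not explain the gap.

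**Step 2: what reproduces the printed figure.** With K = 50 per arm (400 per arm, 98 df), SE = 8.3 × √(2 × 1.14/400) = 0.627, noncentrality = 3.19 and power = 0.885.

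**Step 3: the rows that discriminate** (power at ICC 0/0.02/0.05).

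| Outcome, difference | Printed | 25 cohorts per arm (stated) | 50 cohorts per arm |
|---|---|---|---|
| CES-D 2.0, SD 8.3 | 0.92/0.88/0.83 | 0.66/0.60/0.53 | 0.921/0.885/0.827 |
| CES-D 3.0, SD 8.3 | 0.99/0.99/0.99 | 0.94/0.91/0.86 | 0.999/0.997/0.992 |
| Injection 1.0, SD 4.5 | 0.60/0.57/0.54 | 0.34/0.32/0.30 | 0.595/0.570/0.537 |
| Injection 1.5, SD 4.5 | 0.91/0.89/0.87 | 0.64/0.61/0.58 | 0.910/0.894/0.868 |
| Injection 2.0, SD 4.5 | 0.99/0.99/0.98 | 0.87/0.85/0.82 | 0.993/0.990/0.984 |
| Sex risk 0.25, SD 1.8 | 0.54/0.49/0.43 | 0.28/0.25/0.22 | 0.494/0.445/0.388 |
| Sex risk 0.50, SD 1.8 | 0.98/0.97/0.94 | 0.78/0.72/0.65 | 0.973/0.954/0.917 |

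With 50 cohorts per arm, the CES-D and injection rows agree with print to within about a point. The sex-risk 0.25 row stays 4 to 5 points low at SD 1.8. With SD 1.7 and 50 per arm the two sex-risk rows become 0.540/0.488/0.426 and 0.985/0.971/0.943, which match.

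**Step 4: the 8.3.** As a variance, SD = √8.3 = 2.88. For a 2.0-point difference with 25 cohorts per arm, power is then 1.00 in every column. The printed row is lower, so the table used 8.3 as an SD. The injection table, whose SD is labelled as such, shows the same factor of two and does not depend on this reading.

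**Step 5: other explanations, CES-D 2.0, 25 cohorts per arm** (normal approximation).

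- One-sided test: 0.78/0.73/0.67
- 250 per arm, before attrition: 0.77/0.70/0.61
- 25 cohorts of 16: 0.93/0.85/0.73

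None gives 0.92/0.88/0.83.

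**Step 6: differences detectable with 80% power at ICC 0.02, 48 df.** The required noncentrality is about 2.86.

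- CES-D: 2.86 × 0.886 = about 2.5
- Injection: SE = 4.5 × √(2 × 1.06/100) = 0.655, so 2.86 × 0.655 = about 1.9
- Sex risk: SE = 1.8 × √(2 × 1.14/200) = 0.192, so 2.86 × 0.192 = about 0.55

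**The case against.** **Variance reduction.** The strongest defence is that the authors assumed a smaller working variance without saying so. The section names changes in the outcomes, and the Statistical Analysis Plan section allows covariate adjustment and hierarchical models. Halving the variance with 25 cohorts per arm gives CES-D 2.0 as 0.916/0.878/0.820 and injection 1.5 as 0.904/0.887/0.861, within about a point of print. So the fit alone cannot separate this from 50 cohorts per arm, although the latter fits slightly better (injection 1.0 at ICC 0: 0.595 against 0.586, printed 0.60). What weakens this defence is that the section states no such reduction, gives raw SDs, words the CES-D effect as a post-intervention difference, and would need the same halving for both outcomes.

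**Adjusted analysis.** The figure of 0.60 is for an unadjusted test, and that limit stands. The protocol gives no correlation with baseline. If the variance shrinks by 1 − r², power for 2.0 points at ICC 0.02 is 0.64, 0.72, 0.79 or 0.87 for assumed r of 0.3, 0.5, 0.6 or 0.7. A reader might infer that the trial cannot detect its target effect. The document does not support that: an adjusted analysis could do better, and at 3.0 points even the unadjusted power is about 0.91.

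**Sample size.** The 200 per arm assumes two years of attrition, whereas Study Design and Rationale and Follow-up Visits end follow-up at 12 months. With 250 per arm randomised (Population) and one year at 10%, 225 remain, or 25 cohorts of 9. Power for 2.0 points is then 0.71/0.64/0.56. The replacement figure is therefore not final, but it stays below 0.80.

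**Cause.** A reader might take it as established that 50 cohorts per arm were entered in all three tables. That is an inference from the fit, and the sex-risk table supports it only with an SD of 1.7 that appears nowhere in the text.

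**Conclusion.** The point holds as a failure of the printed powers to follow from the printed inputs, and it should be corrected. For the stated design, an unadjusted cluster t-test at the protocol's expected ICC of 0.02 has power of about 0.60 for 2.0 CES-D points (printed 0.88), 0.61 for 1.5 injection points (printed 0.89) and 0.72 for 0.50 sex-risk points (printed 0.97). The sentence calling 2.0 points sufficient is not supported by the inputs beside it.

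This rests on reading 8.3 as an SD, which the table itself forces, on equal cohort sizes, and on no variance reduction, since none is stated. Entry of the total cohort count as the per-arm count is the likeliest cause but remains an inference. The variance label and the sex-risk SD are separate, smaller errors.

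**What to change.** In Power calculations:

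1. Recompute all three tables with 25 cohorts per arm. If a variance reduction was assumed, state it, give its source and show the tables on that basis.
2. Relabel 8.3 as the SD.
3. Reconcile the sex-risk SD: use 1.8 in the calculation, or correct the stated value.
4. Replace the sentence on sufficient power with the unadjusted power at ICC 0.02 (about 0.60 for 2.0 CES-D points, about 0.91 for 3.0) and the differences detectable with 80% power (about 2.5 CES-D, 1.9 injection, 0.55 sex risk).
5. In the same re-run, reconcile the two-year attrition premise with the 12-month follow-up schedule and update these figures to the resulting sample size.

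The cost is a re-run of the power software and changes to protocol wording. No extra participants are needed; the stated power becomes less favourable.

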For several of our hypotheses, often the individual measures of risk behaviors do not meet linearity assumptions. Use of a composite risk score of risk behavior as the outcome measure has been strongly encouraged by Aral and Peterman (1996), and often addresses the problem of non-linearity. Additionally, transformations, such as taking the square root or natural log, can improve the distribution of the risk behavior variables so that their residuals are distributed approximately normally. As the present study is longitudinal in design and different risk behaviors can change in opposite directions, an indicator of the participant’s overall net risk change is most informative. To test separate hypotheses regarding inject and sexual risk behavior, separate composite scores for each will be generated. The composite score for injection risk behavior will include frequency of sharing needles (without cleaning), cookers, rinse water, and cotton. The composite score for sex risk behavior will include frequency of vaginal sex without a condom, anal sex without a condom, exchanging sex for money or drugs, sex with HIV+, sex with IDU, and number of partners in the past 3 months

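### The power figures for injection and sex risk come from prior-study composites that do not match the composites the protocol says it will analyse

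*Protocol*

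**What the plan says.** The protocol describes each risk composite twice.

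- **As an outcome** (Statistical Analysis Plan, Phase 3). For injection: "The composite score for injection risk behavior will include frequency of sharing needles (without cleaning), cookers, rinse water, and cotton". For sex: "The composite score for sex risk behavior will include frequency of vaginal sex without a condom, anal sex without a condom", followed by exchange sex, sex with an HIV-positive partner, sex with an injector, and number of partners over three months. That makes six named elements. The same paragraph allows a square-root or log transformation.
- **As a planning quantity** (Power calculations). The expected reductions rest on prior data (SHIELD), and the scores behind them are described this way: "creating composite scores for injection risk behavior (needle and cooker sharing and frequency of injecting) and sexual risk behavior (9 risk behaviors". Mean and SD were 11.6 and 4.5 for injection, and 1.9 and 1.8 for sex. The nine sex behaviours are not listed.

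The power tables use differences of 1.0 to 2.5 points (injection) and 0.25 to 1.0 points (sex). For group sizes the section says "A sample size of 200 in each group is assumed for comparisons of sex risk behaviors and depressive symptoms", and for injectors "it is assumed that there will be a sample size of 100 per group with the same attrition rates". Changes in injection risk, sex risk and depressive symptoms are named as the main outcomes.

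**The concern.** Power for a difference in raw points depends on the SD and scale of the score on which the points are counted. If the analysed score has other items, its SD need not be 4.5 or 1.8, and 1.5 or 0.50 points need not mean the same amount of behaviour change. The protocol offers no SD for its own scores, no mapping between the two versions and no reason for the change.

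The definition also affects the conclusion. Suppose the intervention lowers how often people inject but leaves equipment sharing as it was. The planning score then records a benefit and the analysis score records none. Two definitions in one protocol leave it open which result answers the aim on injection risk.

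**Working it through.** **1. Contents side by side**

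| Item | Analysis score | Planning score |
|---|---|---|
| Needle sharing | yes (uncleaned needles) | yes |
| Cooker sharing | yes | yes |
| Rinse water | yes | not named |
| Cotton | yes | not named |
| Injecting frequency | not named | yes |
| Sex risk | 6 named elements | 9, not listed |

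The injection mismatch can be shown item by item. The sex mismatch is seen only in the count.

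**2. Reproducing the stated power with the prior-study SDs**

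Inputs from Power calculations: "We estimated power with a 2-sided test", "setting the alpha at 0.05"; SD 4.5 with 100 per group (injection); SD 1.8 with 200 per group (sex); 25 cohorts per arm of about 8 completers (25 × 8 = 200). Half the sample are injectors, so I take m = 4 injectors per cohort (25 × 4 = 100).

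Formulas (normal approximation): design effect DE = 1 + (m − 1) × ICC; SE = SD × √(2 × DE / n); power ≈ Φ(difference/SE − 1.96).

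- Injection, 1.5 points, ICC 0.02: DE = 1.06; SE = 4.5 × √(2.12/100) = 0.655; 1.5/0.655 = 2.29; power = Φ(0.33) = 0.63. Stated: 0.89.
- Sex, 0.50 points, ICC 0.02: DE = 1.14; SE = 1.8 × √(2.28/200) = 0.192; 0.50/0.192 = 2.60; power = Φ(0.64) = 0.74. Stated: 0.97.

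| Row (ICC 0.00 / 0.02 / 0.05) | Stated | Computed at stated n | Computed at twice n |
|---|---|---|---|
| Injection 1.0 | 0.60 / 0.57 / 0.54 | 0.35 / 0.33 / 0.31 | 0.60 / 0.58 / 0.55 |
| Injection 1.5 | 0.91 / 0.89 / 0.87 | 0.65 / 0.63 / 0.59 | 0.92 / 0.90 / 0.88 |
| Sex 0.25 | 0.54 / 0.49 / 0.43 | 0.28 / 0.26 / 0.22 | 0.50 / 0.45 / 0.39 |
| Sex 0.50 | 0.98 / 0.97 / 0.94 | 0.79 / 0.74 / 0.67 | 0.98 / 0.96 / 0.92 |

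A noncentral t calculation or a one-sided alpha does not close the gap at the stated sizes. The printed injection figures fit SD 4.5 at about 200 per group. The sex figures fit SD 1.8 at about 400 per group for the 0.50 row and only roughly for the 0.25 row. So the tables do appear to rest on the prior-study SDs, but at about double the stated group sizes.

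**3. Power on the analysis scores**

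This cannot be computed, because no SD is given. As an illustration only, assume an SD of 0.75 to 1.5 times the prior-study value, with raw differences held fixed, ICC 0.02 and the stated group sizes:

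| SD multiple | Injection, 1.5 points | Sex, 0.50 points |
|---|---|---|
| 0.75 | 0.86 | 0.93 |
| 1.00 | 0.63 | 0.74 |
| 1.25 | 0.45 | 0.55 |
| 1.50 | 0.33 | 0.41 |

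The right baseline is the 1.00 row, not the printed 0.89 and 0.97. If instead the standardised difference carries over (1.5/4.5 = 0.33 SD; 0.50/1.8 = 0.28 SD), power stays at 0.63 and 0.74 whatever the new SD.

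**The case against.** Planning from a related measure in an earlier study is ordinary practice, and the section says openly that its expected reductions come from SHIELD. If the effect in SD units is similar on both versions, a change of items does no harm. The analysis text also says what each score will include without calling the list complete, and nine sex behaviours could be six elements counted more finely.

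Much of this stands. It rules out several stronger readings that a reader might infer:

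- *That the trial has less power because of the mismatch.* The documents do not support any direction. The gap between 0.63 and 0.89 comes from group size, not from the composites.
- *That a sharing-only score would be mostly zeros.* Injectors do enter on injecting frequency ("Injected drugs more than 3 times in the past week OR"), with no sharing requirement, but the protocol gives no prevalence of sharing.
- *That the sex scores have been shown to differ in content.* The nine behaviours are never named.

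What does not stand is that the mismatch is harmless as written. A proxy is acceptable when it is declared and justified, and here it is neither. An open-ended list does not help either: the planning description of the injection score still lacks two of the analysis items, and an outcome with unstated further items is not defined. Nor is this detail left for a separate analysis plan, since the protocol itself states both definitions.

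**Conclusion.** The point holds as an inconsistency of definition: certain for the injection composite, probable for the sex composite. The printed power for these two main outcomes has not been shown to apply to the scores the trial says it will analyse. Whether true power is higher or lower cannot be determined from the protocol. The mismatch does not touch the CES-D outcome.

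The failure to reproduce is a separate defect, but it limits the remedy: aligning the composites alone would leave the tables wrong. That result assumes 100 and 200 completers per group, about 4 injectors per cohort and a comparison of two means with a simple design effect. A reader might infer that 50 cohorts per arm were entered instead of 50 in total. Doubled group sizes fit that, but the protocol does not show what was entered.

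**What to change.** Before outcome data are seen, give each composite one definition and use it in both sections.

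1. If the prior study collected the items of the analysis scores, rebuild those scores from its data. Report mean and SD on the scale to be analysed, raw or transformed, and restate both power tables. The protocol names only needle sharing, cooker sharing and injecting frequency from that study's injection score, so availability of the other items must be checked.
2. If it did not, either adopt the planning composites as the outcomes, listing all nine sex behaviours, or state power in standardised differences and declare the planning score a proxy with a reason.
3. In either case, run the tables at 100 and 200 per group with the stated cohort numbers, and state the cohort size used for injectors.

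The cost is a short re-analysis of data already used for planning, plus revised wording in two sections. Recruitment and visits need not change, provided the survey holds the items of the definition chosen.
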